## Methods and analysis

### Study design

OASIS is a parallel group, multicentre, randomised controlled trial with a superiority framework and a 1:1:1 individual participant treatment allocation ratio over three study arms. Given the nature of the interventions, blinding healthcare providers, participants or outcome assessors for treatment assignment are not possible. However, data analysis will be performed without knowledge of treatment assignment by coding the treatment arms and unlocking the code only after statistical analysis is completed. Some 17 hospitals, together treating approximately 50% of all haemodialysis patients in the Netherlands, are expected to participate.

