### Secondary study outcomes

#### Complications

Access-related complications requiring pharmacological, surgical or endovascular interventions will be registered from randomisation until the end of the study period or death. Furthermore, the number of days admitted to hospital or visiting outpatient clinics for any reason and for vascular access-related reasons per person-year will be registered. Finally, all-cause mortality from randomisation to the end of the study period will be registered.

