### Quality and safety

Data are entered on electronic case report forms by trained investigators using numerical codes that cannot be traced to the individual subjects. The subject identification code list is kept by the principal investigator at each study site. Any serious adverse events that may occur will be reported to the principal investigator without undue delay after obtaining knowledge of the events. To evaluate differences in serious adverse events and mortality between treatment arms, an interim safety analysis will be performed and presented to a data safety monitoring board every 6 months. Significant differences on safety outcomes may lead to discontinuation of the trial. Furthermore, an independent monitor will be appointed to assess trial processes and data.

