### Data analysis plan

The access-related intervention rates will be analysed using a general linear model with Poisson distribution and identity link, and with time as off-set variable. Both intervention (ie, the prosthetic arteriovenous graft and central venous catheter) groups will be compared with the usual care (autologous arteriovenous fistula) group. Non-adherence to the allocated treatment group is expected as patients cross over to another surgical strategy for vascular access when the randomised strategy is no longer feasible. The primary analysis will be on the intention-to-treat population. Exploratory on-treatment analyses will be performed as well. A subgroup analysis will be performed for patients who had already started haemodialysis using a catheter before inclusion.

Formal statistical comparisons will be made for the following secondary study outcomes:

SF-12/DSI and SF-VAQ summary scores using generalised estimating equations.The number of access-related serious adverse events per person-year using general linear models with Poisson distribution and mortality using Cox regression.The number of days admitted to the hospital or visiting outpatient clinics for any reason per person-year using Student’s t-tests.

Primary outcome data are not expected to be missing, as interventions on vascular access will be reported in the patients’ medical files. We expect little to no loss to follow-up since study participants will be observed three times per week in the dialysis unit and the trial requires no additional study visits. PROMs will be analysed using generalised estimating equations that allow for missing data. Other missing data will be handled by using 10 imputation cycles with regression methods, performing standard analyses for each imputation cycle and considering the variability across the imputation cycles in the final analysis.

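### The only serious-adverse-event rate in the formal final comparisons is restricted to events labelled access-related in an unblinded trial, so it is open to differential attribution; add the all-cause rate beside it

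*Protocol article*

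**What the plan says.** The Data analysis plan introduces its list with "Formal statistical comparisons will be made for the following secondary study outcomes". The entries are patient-reported scores, then "The number of access-related serious adverse events per person-year using general linear models with Poisson distribution and mortality using Cox regression", then "The number of days admitted to the hospital or visiting outpatient clinics for any reason per person-year using Student’s t-tests". The Complications section makes clear that the mortality outcome is all-cause: "all-cause mortality from randomisation to the end of the study period will be registered".

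On blinding, Study design says that "blinding healthcare providers, participants or outcome assessors for treatment assignment are not possible". The safeguard it offers is at the analysis stage: "data analysis will be performed without knowledge of treatment assignment by coding the treatment arms".

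On collection, Quality and safety is not limited to access-related events: "Any serious adverse events that may occur will be reported to the principal investigator without undue delay". The six-monthly look for the data safety monitoring board carries no such limit either: "To evaluate differences in serious adverse events and mortality between treatment arms, an interim safety analysis will be performed". That section adds that significant safety differences may end the trial.

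**The concern.** Whether an event is access-related is a causal judgement, and here the suspected cause is the randomised treatment. Whoever makes that judgement cannot be blinded, and the Introduction records the prevailing expectation that catheters carry more bloodstream infection and death. Bacteraemia without a proven source is the obvious case in which that expectation could decide the label: assigned to the line in a catheter patient, assigned elsewhere in a fistula patient. Coding the arms for the analyst comes too late, because the label is already in the data.

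The stakes are set by the Ethics section, which defends randomising to catheters largely on infection and mortality and criticises earlier evidence as distorted by selection. If the trial's one event-rate comparison of serious harm depends on an unblinded label, an apparent catheter excess could be an artefact, and a real one could be dismissed as an artefact. Serious events without the attribution filter are reported and compared by arm during the trial, yet the corresponding rate is absent from the final formal list.

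**Working it through.** The plan states no figure on this point, so there is none to reproduce. The check has two parts.

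**1. What each harm measure depends on**

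| Measure | Where compared | Needs attribution? | Limitation for serious infection |
|---|---|---|---|
| Access-related serious adverse events per person-year | Final, formal | Yes | Label given with the arm known |
| All-cause mortality | Final, formal | No | Misses non-fatal events; the Ethics section itself cites 1% fatality for catheter-related bloodstream infections |
| Any-reason hospital or outpatient days | Final, formal | No | Pools admissions with outpatient visits |
| Serious adverse events, no stated restriction | Interim, six-monthly | No | Not in the final formal list |

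The gap is therefore specific: no final serious-event rate is free of attribution.

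**2. How much differential attribution could matter (illustration)**

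Inputs from the article: 65 patients per arm, 2 years of recruitment, close-out when the last patient has 1 year of follow-up, and expected median survival of 2.2 years.

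Assumed inputs: uniform accrual and exponential survival; clearly access-related serious events at 0.3 per year in both arms; serious infections of uncertain source at the same true rate r in both arms; a two-sided 5% test with Poisson variance. The shares of uncertain infections labelled access-related are p in the catheter arm and q in the fistula arm.

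Person-years: λ = ln 2 / 2.2 = 0.315. Follow-up is limited to between 1 and 3 years, so the mean is (1/λ)[1 − (e^(−λ) − e^(−3λ))/(2λ)] = 1.456 years. Per arm this is 65 × 1.456 = 94.6 person-years.

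Spurious difference = r(p − q). SE = √[(rp + rq + 0.6)/94.6]. z = difference/SE. False-positive rate = Φ(z − 1.96) + Φ(−z − 1.96).

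| r per year | p / q | Difference per year | z | False-positive rate |
|---|---|---|---|---|
| 0.1 | 60% / 40% | 0.02 | 0.23 | 6% |
| 0.1 | 80% / 40% | 0.04 | 0.46 | 7.4% |
| 0.1 | 80% / 20% | 0.06 | 0.70 | 10.7% |
| 0.2 | 60% / 40% | 0.04 | 0.43 | 7% |
| 0.2 | 80% / 40% | 0.08 | 0.85 | 13.6% |
| 0.2 | 80% / 20% | 0.12 | 1.30 | 25.7% |
| 0.4 | 60% / 40% | 0.08 | 0.78 | 12% |
| 0.4 | 80% / 40% | 0.16 | 1.50 | 32.2% |
| 0.4 | 80% / 20% | 0.24 | 2.33 | 64.6% |

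With p = q the difference is zero and the rate is 5%. With 65 person-years per arm, the 80% rows fall to 7–9%, 11–19% and 24–49% for the three values of r. A lower rate of clear events (0.1–0.2 per year), 65 to 95 person-years and shares from 60%/40% to 80%/20% give 6–85%. The result is driven almost entirely by the assumed shares and by r.

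**The case against.** The strongest reply is that limiting a secondary harm endpoint to events the access could cause is a defensible choice, since all-cause mortality and any-reason days stand beside it. An admission for sepsis enters the days count whatever source is assigned. This stands as far as it goes: a reader might infer that the plan has no attribution-free harm comparison, and that would be wrong. For the reasons in the first table, though, neither measure replaces a serious-event rate.

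A reader might also infer that the comparison is biased as a matter of fact. The documents do not support that. The article does not say who decides access-relatedness or by what criteria, and such rules may be in the full protocol, which is not shown. Their absence from the article is not a fault. A rule would reduce the risk, but it would neither blind the judgement nor put the all-cause rate in the list.

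The upper illustrations should not be leaned on. The Ethics section cites 1.0 catheter-related bloodstream infection per 1000 catheter days, or 0.365 per catheter-year, and describes the risk as lower in the elderly. With r = 0.4 and p = 80%, uncertain-source infections alone would give 0.4 × 0.8 = 0.32 per year in the catheter arm, nearly all of that cited rate. Whole-arm shares also ignore catheter time in the fistula arm: the inclusion criteria admit patients already dialysing by catheter, and the Interventions section does not count temporary catheter use as crossover. That narrows any gap.

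Finally, it is tempting to require that a harm conclusion also hold in the all-cause count. That could hide real harm. Assume a true excess of 0.24 access-related events per year and 94.6 person-years per arm. Power is Φ(0.24/√[(0.30 + 0.54)/94.6] − 1.96) = 72% on access-related events with a base of 0.3 per year. It is only about 34% or 25% on all-cause events with a base of 1.0 or 1.5 per year. This objection stands in full, and no such requirement is proposed.

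**Conclusion.** The point holds as a risk in a choice the article fixes. The one serious-adverse-event rate compared formally at the end depends on a causal label given in an unblinded trial, while the unrestricted events are already reported and compared by arm at interim. Bias against catheters is plausible for infections of uncertain source, but it is not documented. The illustrated false-positive rates (about 6% to 65% in the main table, 6% to 85% over wider assumptions) show only that the error exceeds 5% whenever attribution differs by arm. They rest on assumed event rates, attribution shares and Poisson variance, and are not an estimate for this trial. The primary outcome and the sample size are unaffected.

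**What to change.** In the Data analysis plan, add to the formal secondary comparisons:

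- all serious adverse events per person-year, by arm, intention-to-treat;
- where they can be identified among the reported events, serious bloodstream infections per person-year whatever the attributed source, by arm, intention-to-treat.

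Keep the access-related rate and present the three side by side. State that they will be interpreted together, and that significance in the all-cause count is not a condition for concluding that harm differs.

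The cost is a change of wording and one or two further models. The all-cause rate uses reports already collected under Quality and safety; the infection count depends on what those reports record. The downside is that all-cause counts are noisier because of comorbidity and have less power for access-specific harm, which is why the access-related rate stays.

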BMI (kg/m^2^) (median, %)††		
<21	13	18
22–25	43	35
25–30	33	33
>30	10	14
Central Venous Catheter at dialysis initiation (%)	23	42

*Ischaemic heart disease was defined as a history of angina pectoris or myocardial infarction.

†Vitamin K antagonist use was used as a proxy for cardiac dysrhythmia.

‡Respiratory disease was defined as the need to take pulmonary medication on a daily basis.

§Psychiatric disorder was defined as dementia, depression or other psychiatric disease.

¶The Karnofsky score was used as a proxy for mobility, where a score of >60 was considered as ‘walks without help’, a score of 50–60 as ‘needs assistance for transfers’ and a score of <50 as ‘totally dependent for transfers’.

**32% of the data concerning mobility was missing in the Dusseux cohort.

††29% of the data concerning BMI was missing in the Dusseux cohort.

BMI, body mass index; NECOSAD, Netherlands Cooperative Study on the Adequacy of Dialysis.

Each individual’s risk score was calculated with the original point system as presented by Dusseux (online supplemental data 1). Risk scores ranged from 0 to 28, with a higher score corresponding to a higher risk of mortality. From the individual risk scores, the discrimination for mortality within 2 years was assessed by c-statistics that were pooled over the 10 imputation datasets according to Rubin’s rules.^22^ The Dusseux mortality risk score had a c-statistic of 0.68 (95% CI 0.63 to 0.73) in the NECOSAD validation cohort. Furthermore, the cohort was divided into five groups with increasing mortality risk. A calibration plot of predicted versus observed mortality risk was computed. Calibration was moderate as the model tended to overpredict the mortality risk (53% average predicted risk and 38% average observed risk, figure 2). Finally, we determined a sensible cut-off point for identifying a subset of patients with an unusually long life expectancy. A cut-off between a score of ≤4 and ≥5 was chosen to separate patients with unusually good outcomes (consisting of 22% of patients in the validation cohort with a median survival of 5.0 years, 95% CI 4.3 to 5.4) from elderly haemodialysis patients with a poor life expectancy (consisting of the remaining 78% of patients in the validation cohort with a median survival of 2.2 years, 95% CI 1.9 to 2.5; figure 3).

10.1136/bmjopen-2021-053108.supp1Supplementary data

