#### Patient-reported outcome measures

Short-Form Health Survey (SF-12) and the Dialysis Symptom Index (DSI) measure generic health-related quality of life as well as disease-specific symptom burden.^26^
^27^
The Short-Form Vascular Access Questionnaire (SF-VAQ) measures haemodialysis patients’ satisfaction with their vascular access.^28^
The 5-Level EuroQol 5-Dimensional Questionnaire (EQ-5D-5L) measures health-state utility values.^29^

The SF-VAQ will be administered on a monthly basis, whereas the SF-12, DSI and EQ-5D-5L will be administered at 3-month intervals. To lower their burden, participants who have started haemodialysis treatment will receive the questionnaires during these treatments and will get assistance from a nurse. The questionnaires will be administered from randomisation until the 1 year after study or dialysis initiation, whichever is later.

Other outcome measures will be registered for exploratory analyses and are defined according to the ESVS guidelines on vascular access^5^:

Primary, assisted primary, secondary and functional patency of vascular access.Time until vascular access maturation (definition according to the American Society of Nephrology).^30^
Time until functional vascular access.The number of haemodialysis sessions with inadequate haemodialysis dose (Kt/V) and with cannulation difficulties or failure. Cannulation difficulties or failures will be recorded with the use of monthly questionnaires asking dialysis nurses whether more than one cannulation attempt was required, whether two-needle cannulation was impossible or if cannulation was painful.

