### Sample size calculation

Sample size was estimated for the primary study outcome of access-related intervention rates. Since two intervention groups will be compared with the usual care group, we used Bonferroni correction to account for multiple comparisons, which resulted in an alpha of 0.025. The average number of interventions per year for patients receiving an autologous arteriovenous fistula has previously been reported at 2.48 interventions per year.^31^ The clinically relevant effect size was considered to be one percutaneous intervention per year and 0.5 surgical interventions per year. Since these interventions occur at a ratio of 1.0:0.7,^31^ a reduction of the overall intervention rate by 0.80 interventions per year was used as the clinically relevant effect for sample size calculations.

With these assumptions, a total number of 195 patients (65 patients in each treatment arm) with 1 year of follow-up achieves 80% power to detect a 0.80 decrease in the number of access-related interventions per person-year of haemodialysis treatment between the intervention groups and the usual care group using a two-sided, large-sample z-test of the Poisson event–rate difference at a significance level of 0.025.^32^

Since the study includes patients with a limited life expectancy, a substantial proportion of participants are expected to die before contributing 1 year of follow-up. To compensate for the resulting loss of statistical power, the trial has a variable follow-up with trial closeout for all patients at the time when the last patient enrolled has 1 year of follow-up. Since participant recruitment is expected to take 2 years, the resulting additional follow-up time will more than compensate for the loss of follow-up due to patient mortality in the first year of the study period.

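### The PROM analysis relies on unweighted GEE to deal with missing scores; this is safe only if missingness is completely random or explained by model covariates

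*Protocol article*

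**What the plan says.** In the protocol article, the Data analysis plan lists the PROMs among the secondary outcomes for formal comparison: "SF-12/DSI and SF-VAQ summary scores using generalised estimating equations". On missing data it says "PROMs will be analysed using generalised estimating equations that allow for missing data". The next sentence turns to everything else: "Other missing data will be handled by using 10 imputation cycles with regression methods". PROM scores are therefore left out of the imputation. The section gives no weighting, missingness assumption, working correlation or baseline adjustment for PROMs.

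The schedule is under Patient-reported outcome measures: "The SF-VAQ will be administered on a monthly basis, whereas the SF-12, DSI and EQ-5D-5L will be administered at 3-month intervals". On duration: "The questionnaires will be administered from randomisation until the 1 year after study or dialysis initiation, whichever is later".

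Two statements bear on how much will be missing. Under Sample size calculation, "a substantial proportion of participants are expected to die before contributing 1 year of follow-up". Under Data analysis plan, "We expect little to no loss to follow-up since study participants will be observed three times per week in the dialysis unit".

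**The concern.** The sentence on PROMs gives the choice of GEE as the answer to missing scores. It is true that GEE can be fitted to incomplete series. That does not make the estimates valid. An unweighted GEE solves its equations on the observed scores, and those equations are in general unbiased only if being observed does not depend on the scores, given the covariates in the model. If patients who scored poorly last time are less likely to complete the next questionnaire, the observed means drift upwards. If that drift differs between arms, so does the comparison, in favour of the arm that loses its worse-scoring patients.

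Greater patient satisfaction is one of the three hypotheses stated at the end of the Introduction, so these comparisons will carry weight. The population is old and frail. The arms are open label and differ in timing and in burden. The plan already contains a tool that would relax the assumption, and assigns it to other variables.

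**Working it through.** The article gives no figure for PROM missingness, PROM power or PROM bias, so there is nothing to reproduce. The check has three parts.

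**1. How many series will be cut short by death.** Input: External validation of a mortality prediction model, "the remaining 78% of patients in the validation cohort with a median survival of 2.2 years, 95% CI 1.9 to 2.5". Assuming exponential survival, the proportion dead at 1 year is 1 − 0.5^(1/median):
- median 2.2 years: 1 − 0.5^(1/2.2) = 0.27, and 65 × 0.27 ≈ 18 patients per arm;
- median 2.5 years: 0.24; median 1.9 years: 0.31.

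This is truncation by death. It is not a non-response rate among the living, for which the article gives no number.

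**2. Bias of GEE by dropout mechanism.** Assumed inputs: 6,000 patients per arm, so that bias can be told from noise; scores at 0, 3, 6, 9 and 12 months; SD 10; no true difference; true correlation exchangeable at 0.6; dropout driven by the last observed score. About 25-27% were missing at month 12, except 43% in one arm of the third scenario. Baseline was part of the outcome vector. Under independence working correlation it does not inform the month-12 estimate, so that column is in effect unadjusted. The complete data gave a chance difference of −0.27 points. Bias = (estimate + 0.27)/10, in SD units.

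| Dropout mechanism | Independence: estimate | Bias (SD) | Exchangeable: estimate | Bias (SD) |
|---|---|---|---|---|
| Completely random | −0.21 | 0.01 | −0.07 | 0.02 |
| Score-dependent, same in both arms | −0.38 | −0.01 | −0.18 | 0.01 |
| Same dependence, more dropout in one arm (43% v 25%) | +0.49 | 0.08 | −0.19 | 0.01 |
| Score-dependent in one arm only | −1.56 | −0.13 | −0.20 | 0.01 |
| Opposite dependence in the two arms | −2.77 | −0.25 | −0.27 | 0.00 |

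Simulation error for a complete-data difference is √(2/6000) ≈ 0.018 SD, so entries of 0.02 or less are noise. With an autoregressive true correlation of 0.8 the independence column was almost unchanged (0.07, −0.13 and −0.25 SD in the last three rows). The exchangeable column, now misspecified, stayed within about 0.04 SD.

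**3. What the baseline score does.** Assumed inputs: correlation 0.7, about 30% missing, score-driven dropout in one arm only. Absolute bias at month 12:
- independence GEE, no baseline adjustment: 0.15-0.25 SD;
- independence GEE, baseline as covariate: 0.05-0.07 SD (0.02-0.04 SD under other settings);
- correctly specified exchangeable GEE using baseline: about 0.02 SD;
- same dropout mechanism in both arms: at most about 0.03 SD.

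With exchangeable GEE and baseline left out altogether, one such run gave 0.10 SD. Much of the difference between a bad and a good GEE is therefore the use of the baseline score.

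**The case against.** The strongest case against the point has five parts.

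- **Arm-specific dropout is conjecture.** The large figures need score-dependent dropout that differs between arms, and nothing in the article shows it. With the same mechanism in both arms the contrast is nearly unbiased. This stands, and it is why the point is conditional.
- **Non-response among survivors is limited by design.** Questionnaires are given during dialysis with a nurse's help, and little loss to follow-up is expected. This stands for patients on dialysis. It does not cover patients randomised up to 6 months before their expected start.
- **Death is a different problem.** A reader might take the roughly 27% first-year mortality as missing data that GEE mishandles. The article does not support that reading: a score after death is undefined, not missing. For the mean among those alive, GEE with independence working correlation is a recognised choice.
- **A mixed model is not simply better.** A reader might infer that GEE should be replaced because a likelihood-based mixed model is valid under missing at random. With death in the data, that model implicitly extrapolates past death, which conflicts with a while-alive reading. The gap between the methods also narrows greatly once both use the baseline score.
- **Detail belongs in the analysis plan.** Working correlation and baseline adjustment are commonly left there, and their absence from an article is no fault. What remains is that the article itself fixes the method, gives its reason, and assigns imputation elsewhere.

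**Conclusion.** The point holds in a limited form. The article treats GEE as sufficient for missing PROM scores, and as a general statement that is wrong. The secondary PROM comparisons can be biased if non-response among living patients depends on earlier scores and differs by arm.

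As an illustration, the size is roughly 0.1-0.25 SD for independence GEE without baseline adjustment, about 0-0.07 SD once the baseline score is used, and near zero if dropout works alike in both arms. These figures rest on assumed correlations, dropout slopes and 25-30% missingness (43% in one arm of one scenario), a rate that the article does not state for living patients. If non-response among survivors is as low as the article expects, the bias will be smaller.

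The documents do not support saying that the PROM results will be biased, that one arm will be favoured, or that GEE must be abandoned. PROMs are secondary and the primary outcome is unaffected. The change is still worth making because a better method is already in the plan.

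**What to change.** In the Data analysis plan or the statistical analysis plan, before arm-level data are seen:

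- Extend the planned 10-fold multiple imputation to PROM scores missing while the patient is alive, with earlier scores and arm in the imputation model. Inverse-probability weighting of the GEE is an equivalent route.
- Include the baseline score in the GEE and name the working correlation. A baseline SF-VAQ score may not exist for patients not yet dialysing, who by the exclusion criteria have no patent fistula or graft. For them the imputation or weighting has to do the work.
- Impute nothing after death, state that scores are interpreted while alive, and report mortality by arm beside the PROM results.
- State the missingness assumption. A likelihood-based mixed model is an alternative for missingness among survivors, provided the while-alive reading is kept.

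The cost is slight extra analysis work, with no added visits, patients or data.

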### Economic analysis

A cost effectiveness analysis and a budget impact analysis comparing the different treatment strategies will be performed by collecting financial data from randomisation until the 1 year after study or dialysis initiation, whichever is later. The economic analyses will be done according to Dutch national guidelines and have a time horizon of 2 years that corresponds to the median life expectancy of the trial participants.^33^

For the cost effectiveness analysis, we will consider both healthcare sector costs and costs for patients and their families. Due to the age of our study population, absenteeism in paid work and production losses in the domestic sphere will not be considered. The relevant cost factors for the healthcare sector will be derived from hospital and pharmacy registration systems at the individual participant level. Costs to patients and families will be measured using a study-specific adaptation of the Medical Consumption Questionnaire developed by the Institute for Medical Technology Assessment at 3 month intervals.^34^ After measurement of the relevant cost factors, monetary values will be assigned.

The budget impact analysis will be performed to estimate the financial consequences for the Dutch national healthcare budget for the different vascular access strategies in elderly haemodialysis patients. The perspectives that will be included in the analysis are the wider societal perspective including productivity losses, the narrower perspective of the public, and the perspective of healthcare providers and health insurance companies. Several scenarios will be included to assess the impact of different reimbursement options.

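### Ten imputations are fixed whatever the amount missing: harmless for record-based outcomes, but avoidable simulation noise in questionnaire-based patient and family costs if these are substantially incomplete

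*Protocol article*

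**What the plan says.** The protocol article's Data analysis plan divides missing data into three classes.

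- Primary outcome: "Primary outcome data are not expected to be missing, as interventions on vascular access will be reported in the patients’ medical files".
- Patient-reported outcomes: "PROMs will be analysed using generalised estimating equations that allow for missing data".
- Everything else: "Other missing data will be handled by using 10 imputation cycles with regression methods", followed by "performing standard analyses for each imputation cycle and considering the variability across the imputation cycles in the final analysis".

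On attrition it adds: "We expect little to no loss to follow-up since study participants will be observed three times per week in the dialysis unit". No percentage of missing data is given for any variable, and no reason for choosing ten.

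The residual class can include the hospital-day comparison, listed as "The number of days admitted to the hospital or visiting outpatient clinics for any reason per person-year using Student’s t-tests", and the inputs to the cost-effectiveness analysis. Under Economic analysis these inputs have two sources. For the healthcare sector: "The relevant cost factors for the healthcare sector will be derived from hospital and pharmacy registration systems at the individual participant level". For patients and families: "Costs to patients and families will be measured using a study-specific adaptation of the Medical Consumption Questionnaire", administered every 3 months.

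**The concern.** The random error that comes from using a finite number of imputations depends on the fraction of missing information and on the number of draws. A number fixed in advance, without regard to the amount missing, may be ample for one variable and thin for another.

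The patient and family cost questionnaire is where it could be thin. A cumulative cost is built from repeated waves, so a single missed wave leaves a participant's total incomplete. The article's reassurance rests on attendance at the dialysis unit. Attendance limits loss to follow-up, but it does not rule out unanswered questionnaires. It also does not yet apply to participants randomised up to 6 months before dialysis starts, as the Inclusion criteria allow. Costs matter to the trial, since lower healthcare costs are part of the hypothesis in the Introduction.

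At stake is the stability of the estimate for that one cost component and of its interval.

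**Working it through.** **Inputs**

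- Number of imputations m = 10 (Data analysis plan).
- Comparison value m = 50, chosen here as an example.
- FMI: not in the document. Assumed 2 to 10% for record-based data, in line with the little loss to follow-up that the article expects, and 0.2 to 0.4 for a substantially incomplete questionnaire.

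The article derives no figure for the ten imputations, so there is nothing to reproduce. The sample size does not enter these formulas.

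**Formulas**

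- The between-imputation variance is FMI times the total variance. The mean of m draws therefore has a Monte Carlo standard deviation, as a share of the standard error (SE), of sqrt(FMI/m).
- Variance inflation relative to infinitely many imputations is FMI/m.
- Relative efficiency is 1/(1 + FMI/m).

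**Record-based outcomes, m = 10**

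| Assumed FMI | Monte Carlo error / SE | Relative efficiency |
|---|---|---|
| 2% | sqrt(0.02/10) = 0.045 | 99.8% |
| 5% | sqrt(0.05/10) = 0.071 | 99.5% |
| 10% | sqrt(0.10/10) = 0.100 | 99.0% |

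At most about 1% of efficiency is lost, and the SE grows by 0.5% or less.

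**Questionnaire-based patient and family costs**

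| Assumed FMI | Monte Carlo error / SE, m = 10 | m = 50 | Variance inflation, m = 10 | m = 50 |
|---|---|---|---|---|
| 0.2 | 0.141 | 0.063 | 2% | 0.4% |
| 0.3 | 0.173 | 0.077 | 3% | 0.6% |
| 0.4 | 0.200 | 0.089 | 4% | 0.8% |

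Moving from 10 to 50 reduces the Monte Carlo error by 1 − sqrt(10/50) = 55% at any FMI. The gain in interval width is small: at FMI 0.4 the SE is inflated by sqrt(1.04) − 1 = 2.0% with 10 imputations, against sqrt(1.008) − 1 = 0.4% with 50.

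**Total incremental cost.** The rows above apply to the questionnaire component alone. The total adds healthcare-sector costs from registration systems. If these dominate the variance of the total and are nearly complete, the FMI of the total is lower, and so is its Monte Carlo error. The article gives no figures from which to compute that share.

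**The case against.** The case for leaving the text alone is strong on most points.

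- **The higher FMI is assumed.** The article expects little loss to follow-up. Under Patient-reported outcome measures, it also has nurses assist with those questionnaires during dialysis. If the cost questionnaire is handled in the same way, non-response may be low. This stands, and it is why the point is conditional.
- **Pooling is valid with ten.** The plan carries the between-imputation variability into the final analysis. This stands: the issue is avoidable noise and slight inefficiency, not wrong inference.
- **Fifty is not derived from the document.** This is true. A rule that only matched m to the percentage of incomplete cases would accept ten when up to 10% are incomplete. The floor of 50 is a convenience that costs almost nothing.

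A reader might go further and infer that the hospital-day comparison would be unstable. The documents do not support that. These days are registered throughout follow-up (Secondary study outcomes, Complications), and nothing suggests that much of this information would be missing.

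A reader might also infer that two analysts could reach opposite verdicts on costs. The arithmetic for that is easy to produce. With FMI 0.3 to 0.4 and a statistic of 2.16 judged against 1.96, the chance that one run falls below the line is Φ(−0.20/0.173) = 0.124 to Φ(−0.20/0.200) = 0.159. Two seeds would then disagree in 2p(1 − p) = 22 to 27% of pairs. But the article lists no formal test of costs and sets no significance threshold for them, so there is no such verdict to flip. A result close enough to a threshold can also change with any finite number of imputations: at 2.06 and m = 50, the same formula still gives 18 to 23%.

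**Conclusion.** The point holds in a narrow form. Fixing ten imputations regardless of the amount missing leaves avoidable simulation noise in one place, the patient and family cost component, and only if that questionnaire is substantially incomplete. Under an assumed FMI of 0.2 to 0.4, the noise is 0.14 to 0.20 SE, against 0.06 to 0.09 SE with 50 imputations. The effect on total incremental cost is smaller if registry-based costs dominate.

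For record-based outcomes the effect is negligible at an FMI of 10% or less. The primary outcome is not expected to be missing, and patient-reported outcomes go to generalised estimating equations, so neither depends on the ten imputations. This is not an error or a contradiction in the plan. It is a refinement of the lowest severity, and the size given rests on a missing fraction that the article does not state.

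**What to change.** In the Data analysis plan, replace the fixed ten cycles with at least 50 imputations, or with a number equal to the percentage of incomplete cases if that is larger. For example: *Other missing data will be multiply imputed by regression methods, using at least 50 imputations or as many as the percentage of incomplete cases, whichever is larger.* The pooling step stays as it is.

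The change takes a few words and some computing time, which is trivial for 195 participants. It needs no extra data or patients. If missingness proves low, nothing is lost.
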